## 8.2 CART+4W, CART+12W – CART FOLLOW-UP VISITS (4 AND 12 WEEKS AFTER CART RESUMPTION)

As when naïve HIV positive individuals start 1st line treatment, all individuals will be followed to monitor clinical, virological and immune outcomes after cART resumption.

Following procedures will be performed:

- Blood extraction including:
  - Viral load, biochemistry and hematological parameters and CD4 count
  - Plasma and PBMC storage following scheme detailed in attachment K

- Clinical visit, adverse event register
- cART adherence assessment (SERAD questionnaire)
- Next visit scheduling
- CRF data collection

### **8.2.1 cART+24w – end of trial visit (24 weeks after cART resumption)**

Following procedures will be performed:

- Blood extraction including:
  - o Viral load, biochemistry and haematological parameters and CD4 count
  - o Plasma and PBMC storage following scheme detailed in attachment K
- Clinical visit, adverse event register
- cART adherence assessment (SERAD questionnaire)
- Explain to the patient that the study is finished. Schedule visits with regular physician according to routine clinical practice.
- CRF data collection

### **8.3 LONG-TERM FOLLOW-UP**

After end-of-study, participants will continue with cART and return to standard clinical care in consultation with their doctor, in HIV units from HGTIP and HC. All participants will be followed-up annually for 5 years in regards to:

- Safety
- HIV related information
- Gene transcription studies

### **8.4 PROCEDURES FOR EVALUATION OF RESPONSE**

#### **8.4.1 Clinical record and physical exam**

Demographic and HIV infection-related data will be collected in order to characterize the study population (sex, age, time since HIV transmission to treatment initiation, Fiebig stage at HIV diagnosis, risk factor and history of opportunistic infections or tumors).

Appearance of clinical adverse events will be recorded all over the study. Appearance of acute retroviral symptoms (Fever of unknown origin, Headache, Pharyngitis, Lymphadenopathy, Myalgia/arthritis, Night sweats, Fatigue, Nausea, vomiting, Hepato/splenomegaly, Rash, Diarrhea, Others) will be specifically recorded during the MAP phase.

A complete physical examination will be performed at the baseline visit, including weight and height. In the follow-up visits, a physical exam will be performed following schedule described in attachment J (Schedule of procedures).

#### 8.4.2 Laboratory tests

Patients will fast for at least 8 hours prior to assessment, in the points specified in the schedule of procedures of the study (attachment J), except for RMD1 assessment that will be performed in the evening previous RMD1 administration. The following parameters will be quantified, as needed:

- **Hematology:**
  - Hematocrit
  - Red blood cell count
  - Hemoglobin
  - Leucocytes
  - Lymphocyte
  - Platelet count
- **Blood biochemistry:**
  - Urea
  - Creatinine
  - Ionogramme: sodium, potassium
  - Total Bilirubin
  - Total protein
  - Albumin
  - Liver enzymes: aspartate aminotransferase (AST), alanine aminotransferase (ALT), gamma-GT, alkaline phosphatase
  - Estimated glomerular filtration rate (CKD-EPI)
  - Creatinin Kinase (CK)

**Extra ions:** Magnesium, phosphate and calcium

- **Pregnancy test in women (test strip)**
- **Immunology:**
  - CD4 lymphocytes count
  - CD4 lymphocytes percentage
  - CD8 lymphocytes count
  - CD8 lymphocytes percentage

**Note:** Before the beginning of the study, all labs will facilitate to the sponsor and to the investigator a list of the reference normal values of the parameters assessed.

- **Specific Lab Procedures**  
To be assessed along the study, as detailed in the endpoint section 5.3:
  - Romidepsin concentrations in plasma will be determined by liquid chromatography–mass spectrometry (LC-MS) / mass spectrometry (MS)
  - HIV-1 DNA in CD4 T cells by ddPCR
  - Cell-associated RNA (CA-RNA)

- Viability, necrosis and apoptosis levels by flow cytometry
- Activation, exhaustion and proliferation capacity by flow cytometry
- IFNg production assessed by ELISPOT
- In-vitro viral inhibition capacity
- Ultrasensitive plasma viral load (SCA)
- Histone H3 acetylation in lymphocytes

### 8.4.3 Electrocardiogram

Electrocardiogram changes have been described in trials using romidepsin at oncologic doses. EKG leads are attached to the body while the patient lies flat on a bed. Leads are attached to each extremity (four total) and to six pre-defined positions on the front of the chest. A small amount of gel is applied to the skin, which allows the electrical impulses of the heart to be more easily transmitted to the EKG leads. The leads are attached by small suction cups, Velcro straps, or by small adhesive patches attached loosely to the skin. The test takes about five minutes and is painless. During RMD1,2,3 infusions, ECG will be performed to estimate heart rate and detect potential QT prolongation, repolarization abnormalities and/or T wave inversion.

### 8.4.4 Vaccine patient diary

Data on local and systemic events will be solicited with specific diary cards (attachement F) for a minimum of 7 days following each immunization. Following parameters will be collected:

Local Reactogenicity, including:

- Redness (mm)
- Induration (mm)
- Pain (0-4)

General Symptoms, including:

- Temperature (°C)
- Headache (0-4)
- Fatigue (0-4)
- Nausea (0-4)
- Vomiting (0-4)
- Diarrhea (0-4)
- Abdominal pain (0-4)
- Sudoration (0-4)
- Muscular pain (0-4)
- Lack of appetite (0-4)
- Other, describe

0-4 grades intensity, according to the following definitions described at DAIDS:

- 0: No symptoms
- 1: Symptoms causing no or minimal interference with usual social & functional activities.

- 2: Symptoms causing greater than minimal interference with usual social & functional activities
- 3: Symptoms causing inability to perform usual social & functional activities
- 4: Symptoms causing inability to perform basic self-care functions OR Medical or operative intervention indicated to prevent permanent impairment, persistent disability, or death

The investigator will review the patient diary and ensure that proper record has been performed. The severity of each AE will be graded by the investigator. Criteria for grading clinical and laboratory events were based on DAIDS grading table. The investigator will state the relationship of each AE to the vaccination by using prespecified terms including unrelated, unlikely to be, possibly, probably and definitely related to vaccination. In those cases where grading of AE do not coincide with patient's description, a discussion will be registered in the medical record.

#### 8.4.5 Romidepsin patient diary

Data on local and systemic events will be solicited with specific diary cards (attachment G) for a minimum of 7 days following each romidepsin administration. Following parameters will be collected:

General Symptoms, including:

- Temperature (°C)
- Headache (0-4)
- Fatigue (0-4)
- Nausea (0-4)
- Vomiting (0-4)
- Diarrhea (0-4)
- Abdominal pain (0-4)
- Sudoration (0-4)
- Muscular pain (0-4)
- Lack of appetite (0-4)
- Heart palpitations (0-4)
- Rash (0-4)
- Bloating (0-3)
- Metallic Taste (0-4)
- Other, describe

0-4 grades intensity, according to the following definitions:

- 0: No symptoms
- 1: Symptoms causing no or minimal interference with usual social & functional activities
- 2: Symptoms causing greater than minimal interference with usual social & functional activities
- 3: Symptoms causing inability to perform usual social & functional activities
- 4: Symptoms causing inability to perform basic self-care functions OR Medical or operative intervention indicated to prevent permanent impairment, persistent disability, or death

The investigator will review the patient diary and ensure that proper record has been performed. The severity of each AE will be graded by the investigator. Criteria for grading clinical and laboratory events were based on DAIDS scale. The investigator will state the relationship of each AE to the vaccination by using prespecified terms including unrelated, unlikely to be, possibly, probably and definitely related to vaccination. In those cases where grading of AE do not coincide with patient's description, a discussion will be registered in the medical record.

## 9 ADVERSE EVENTS

### 9.1 DEFINITION

**Adverse event:** (AE) Medical event presented by a patient or clinical research subject administered a pharmaceutical product, and which does not necessarily have a causal relation to the treatment.

**Serious adverse event:** (SAE) Medical event classified as such and which, regardless of the dose involved:

- causes patient death,
- produces a life-threatening situation for the patient,
- requires or prolongs in hospital admission,
- produces important or persistent incapacitation/handicap, or constitutes a congenital defect or anomaly,
- needs action to prevent any of above situations.
- is considered medically significant

Examples of such events are intensive care in an Emergency Service or in the home in a patient with allergic bronchospasm; blood dyscrasias or seizures not giving rise to hospital admission, or the development of drug dependency or abuse.

**Unexpected adverse event:** (UAE) AE related to the product in investigation the nature or intensity of which does not coincide with the information available on the product administered (IB or SmPC).

**Serious unexpected adverse reaction:** (SUSAR) SAE related to the product in investigation the nature or intensity of which does not coincide with the information available on the product administered (IB or SmPC).

### 9.2 MONITORING, RECORDING AND REPORTING OF ADVERSE EVENTS

An AE is any noxious, unintended, or untoward medical occurrence that may appear or worsen in a subject during the course of a study. It may be a new intercurrent illness, a worsening concomitant illness, an injury, or any concomitant impairment of the subject's health, including laboratory test values (as specified by the criteria below), regardless of etiology. Any worsening (i.e., any clinically significant adverse change in the frequency or intensity of a pre-existing condition) should be considered an AE. A diagnosis or syndrome should be recorded on the AE page of the CRF rather than the individual signs or symptoms of the diagnosis or syndrome.

An overdose, accidental or intentional, whether or not it is associated with an AE, or abuse, withdrawal, sensitivity or toxicity to an investigational product should be reported as an AE. If an overdose is associated with an AE, the overdose and AE should be reported as separate terms.

All subjects will be monitored for AEs during the study. Assessments may include monitoring of any or all of the following parameters: the subject's clinical symptoms, laboratory, pathological, radiological or surgical findings, physical examination findings, or other appropriate tests and procedures.

All AEs will be recorded by the Investigator from the time the subject signs informed consent until the last study visit or to 28 days after the last dose of IMP in case of early withdrawal while patient is receiving IMP. AEs and SAEs will be recorded on the AE page of the CRF and in the subject's source documents. All SAEs must be reported to the Sponsor (see contact details at the end of the paragraph) within 24 hours of the Investigator's knowledge of the event by facsimile, or other appropriate method, using the SAE Report Form (attachment N, can be found in the Investigator's File), or approved equivalent form.

### 9.3 DOCUMENTATION RELATED TO AE AND SAE

Each AE and SAE to take place during the study should be documented in the medical records of the patient in accordance with standard clinical practice of the researcher, and in the CRF. For each SAE, an independent set of SAE form will be used independently. Only if there are multiple SAE at the time of the initial report and these are temporary and / or clinically interrelated can be registered on the same set of SAE form.

The researcher should try to make a diagnosis of the event based on the signs, symptoms and / or other clinical information. An AE diagnosis has to be recorded per line or a sign/symptom if the diagnosis is not available. If a diagnosis subsequently becomes available, this then should be entered and the sign/symptom crossed out, initialed and dated by the investigator.

SAE pages found in the investigator's file shall be completed as precisely as possible, printed and shall be signed by the investigator before being sent to the sponsor. It is very important that the initial page SAE researcher provide its opinion in regard to the relationship of the event to the study drug.

### 9.4 EVALUATION OF ADVERSE EVENTS

A qualified Investigator will evaluate all AEs as to:

#### 9.4.1 Seriousness

A SAE is any AE occurring at any dose that:

- Results in death;
- Is life-threatening (i.e., in the opinion of the Investigator, the subject is at immediate risk of death from the AE);
- Requires inpatient hospitalization or prolongation of existing hospitalization (hospitalization is defined as an inpatient admission, regardless of length of stay);

- Results in persistent or significant disability/incapacity (a substantial disruption of the subject's ability to conduct normal life functions);
- Is a congenital anomaly/birth defect;
- Constitutes an important medical event.

Important medical events are defined as those occurrences that may not be immediately life threatening or result in death, hospitalization, or disability, but may jeopardize the subject or require medical or surgical intervention to prevent one of the other outcomes listed above. Medical and scientific judgment should be exercised in deciding whether such an AE should be considered serious.

Events **not considered** to be SAEs are hospitalizations for:

- A standard procedure for protocol therapy administration. However, hospitalization or prolonged hospitalization for a complication of therapy administration will be reported as an SAE.
- Routine treatment or monitoring of the studied indication not associated with any deterioration in condition.
- A procedure for protocol/disease-related investigations (e.g., surgery, scans, endoscopy, sampling for laboratory tests, bone marrow sampling). However, hospitalization or prolonged hospitalization for a complication of such procedures remains a reportable SAE.
- Hospitalization or prolongation of hospitalization for technical, practical, or social reasons, in absence of an AE.
- A procedure that is planned (i.e., planned prior to starting of treatment on study); must be documented in the source document and the CRF. Hospitalization or prolonged hospitalization for a complication remains a reportable SAE.
- An elective treatment of a pre-existing condition unrelated to the studied indication.
- Emergency outpatient treatment or observation that does not result in admission, unless fulfilling other seriousness criteria above.

If an AE is considered serious, both the AE page/screen of the CRF and the SAE Report Form must be completed.

For each SAE, the Investigator will provide information on severity, start and stop dates, relationship to IP, action taken regarding IP, and outcome.

#### 9.4.2 Severity / Intensity

For both AEs and SAEs, the Investigator must assess the severity / intensity of the event.

Intensity will be assessed by the investigator using the following terms according to the Division of AIDS table for grading the severity of adult and pediatric adverse events (Attachment O):

- Grade 1 = Mild
- Grade 2 = Moderate
- Grade 3 = Severe
- Grade 4 = Life threatening
- Grade 5 = Death

The term “severe” is often used to describe the intensity of a specific event (as in mild, moderate or severe myocardial infarction); the event itself, however, may be of relatively minor medical significance (such as severe headache). This criterion is *not* the same as “serious” which is based on subject/event *outcome* or *action* criteria associated with events that pose a threat to a subject’s life or functioning.

Seriousness, not severity, serves as a guide for defining regulatory obligations.

#### 9.4.3 Causality

The causal relation will be established according to the algorithm of the Spanish Pharmacovigilance System, which contemplates the following categories:

##### Definitive:

- A plausible time sequence exists in relation to administration of the drug or its plasma or tissue concentrations.
- The observed manifestation coincides with the known adverse reactions profile of the implicated drug.
- The event cannot be explained by the concurrent disease or by other drugs or chemical substances.
- Response to withdrawal must be clinically plausible, i.e., the condition improves on discontinuing administration of the drug.
- A positive response to repeat exposure is observed.

##### Probable:

- A reasonable time sequence exists in relation to administration of the drug.
- The observed manifestation coincides with the known adverse reactions profile of the implicated drug.
- The event is unlikely to be explained by the concurrent disease or by other drugs or chemical substances.

- Response to withdrawal is clinically plausible, i.e., the condition improves on discontinuing administration of the drug.
- No repeat exposure is required to complete this definition.

**Possible:**

- A reasonable time sequence exists in relation to administration of the drug.
- The observed manifestation coincides with the known adverse reactions profile of the implicated drug.
- The event might be attributable to the clinical condition of the patient or to other concomitantly administered drugs or chemical substances.
- Information concerning drug withdrawal may be unavailable or confusing.

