## 5.6 END OF TRIAL

Stopping rules will be based on the observation of an unexpected high proportion of individuals experiencing SAE or any grade  $\geq 3$  local or systemic events judged definitely or probably related to any of the vaccinations and/or romidepsin administration.

If two or more study participants develop a clinically similar SAE or grade 3 local or systemic event, judged definitely, or probably related to the investigational medicinal products (IMP)s, a review by the Scientific Committee will be requested. The study will be suspended pending review of all safety data. Following this review, the Scientific Committee will make a recommendation to the Principal Investigator and Sponsor regarding continuation of the study (see section 9.3 for details)

In addition, if more than 50% of participants withdraw from the Scientific Committee will discuss a premature stop of the trial.

The date of the end of the trial will be to the last visit of the last patient.

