**Unrelated:**

- None of the above criteria are met.

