### 10.3 SAMPLE SIZE DESCRIPTION

Individuals that participated in the BCN01 trial and which are followed in the extension phase (BCN01-RO) will be offered to participate in the study. Therefore, the trial will enroll a maximum number of 24 subjects. The primary endpoint of the study is safety and tolerability of the combined kick & kill strategy in recently HIV-1-infected individuals under early suppressive therapy. In terms of total number of individuals exposed to each MVA.HIVcons vaccine and confidence intervals to detect an AE (i-e- based on published results the probability of experiencing a grade 3 or 4 AE is thought to be <0.1). Information on expected rates of AEs related to RMD at the clinical dose proposed is still scarce. The trial has been designed as a pilot study and will only allow detection of a large effect among participants. However, the incidence of grade  $\geq 3$  or SAEs will be used as a measure of safety of the experimental strategy.

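### The causality scale in section 9.4.3 leaves no related category for a new kind of reaction, contradicting the SUSAR definition and weakening the section 5.6 trigger; section 8.4.5 names the wrong product

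*Protocol*

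**What the plan says.** **Causality scale.** Section 9.4.3 has relatedness decided by the algorithm of the Spanish Pharmacovigilance System, in five categories. Definitive, Probable and Possible each list "The observed manifestation coincides with the known adverse reactions profile of the implicated drug". Probable ends with "No repeat exposure is required to complete this definition". Improbable describes an event whose timing makes a causal link unlikely and for which other explanations are plausible. Unrelated reads "None of the above criteria are met".

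**Unexpected events.** Section 9.1 defines a SUSAR as "SAE related to the product in investigation the nature or intensity of which does not coincide with the information available on the product administered", and words the unexpected adverse event in the same way.

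**Stopping rule.** Section 5.6 first speaks of an unexpectedly high proportion of participants with SAEs or any event of grade 3 or higher "judged definitely or probably related to any of the vaccinations and/or romidepsin administration". It then gives the numeric trigger, which concerns relation to either study product: "If two or more study participants develop a clinically similar SAE or grade 3 local or systemic event, judged definitely, or probably related to". When that is met, the study is suspended pending committee review.

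**Romidepsin diary.** Section 8.4.5 states: "The investigator will state the relationship of each AE to the vaccination by using prespecified terms". The section 10 introduction asks for imputability to both MVA.HIVconsv and romidepsin.

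**Prior information.** Section 10.3 concedes: "Information on expected rates of AEs related to RMD at the clinical dose proposed is still scarce".

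**The concern.** Safety of a new combination is a primary endpoint, and little is known about romidepsin at this dose. A reaction not previously seen is therefore one that the safety system most needs to recognise. If relatedness requires a match with what is already known, such a reaction has no place on the scale. SUSAR classification then rests on two passages that cannot both be followed, and the study-level trigger can miss the event because it depends on a rating that the scale does not allow.

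The sentence in 8.4.5 adds a second attribution problem. Events solicited after each infusion are to be related to the vaccination, although the three infusions come 3, 4 and 5 weeks after the first vaccination and the safety analysis needs attribution to each product.

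**Working it through.** The protocol states no operating characteristic for the stopping rule, so there is no figure to reproduce. The check is mainly textual; the arithmetic only illustrates scale.

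**Step 1: are the lists cumulative?** The protocol does not say so outright. Probable, however, expressly waives repeat exposure as something needed to complete the definition. Waiving one item implies that the remaining items are needed.

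**Step 2: classify a test event.** Take an event of a new kind, with reasonable timing and no better explanation.

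| Category (9.4.3) | Fit | Reason |
|---|---|---|
| Definitive | No | no match with the known profile |
| Probable | No | same |
| Possible | No | same |
| Improbable | No | timing is not unlikely; no alternative explanation |
| Unrelated | Unclear | the event meets at least the timing criterion, so it is not true that it meets no criterion |

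Strictly read, the event has no category.

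**Step 3: compare with 9.1.** A SUSAR must be related and must differ from the product information in nature or intensity. A known reaction of unexpected intensity can still satisfy the profile item. A reaction of unexpected nature cannot. For nature, 9.1 and 9.4.3 contradict each other.

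**Step 4: follow the event to 5.6.** The numeric trigger counts events rated definite or probable. The test event has neither rating and does not count. If it is serious, 9.8.4 still sends it to the coordinating investigator, with no causality filter, so that the committee can be called. If it is a non-serious grade 3 event, that route is absent.

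**Step 5: attribution in 8.4.5.** The sentence names only the vaccination. Sections 5.6, 7.3.2 and 10 all presuppose a judgement about romidepsin. The terms also differ: 8.4.4 and 8.4.5 use unlikely and definitely where 9.4.3 uses Improbable and Definitive.

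**Step 6: grade wording in 5.6.** The general statement covers grade 3 and above; the numeric trigger says grade 3. Grade 4 or 5 events will mostly be serious and so enter through the SAE limb. A non-serious grade 4 laboratory value may not, because 9.5 makes a laboratory abnormality an SAE only if it meets a seriousness criterion, whatever its grade.

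**Step 7: illustration.** Inputs: n = 24, the maximum in 10.3; a trigger of at least two participants, from 5.6; event rate p, which is **assumed**. Section 10.3 gives only a probability below 0.1 for grade 3 or 4 events with the vaccine and no rate for romidepsin. Participants are taken as independent and all events as clinically similar. If a share q of the events is rated definite or probable, then with r = pq

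P(at least 2) = 1 − (1 − r)^24 − 24·r·(1 − r)^23.

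For r = 0.10: 1 − 0.0798 − 0.2127 = 0.7075.

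| Assumed rate p | q = 1 | q = 0.5 | q = 0 (9.4.3 literal) |
|---|---|---|---|
| 5% | 0.34 | 0.12 | 0 |
| 10% | 0.71 | 0.34 | 0 |
| 20% | 0.97 | 0.71 | 0 |

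**The case against.** A reader might infer that new toxicity of the combination can never be called related, that it must be tabulated as unrelated, that SUSAR reporting is void, and that the stopping rule sees only known toxicity. The documents do not support that much:

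- The test event fits no category; it is not forced into Unrelated. That leaves a gap for investigator judgement.
- That the lists are cumulative is an inference, though a sound one. How the Spanish algorithm itself treats unlisted events is not in the document.
- Section 9.1 expressly provides for related unexpected events, and 9.8.1 sets reporting times for SUSARs. This is a conflict between two passages, and neither is stated to prevail.
- All SAEs go to the coordinating investigator under 9.8.4, and the first sentence of 5.6 can be read as covering SAEs of any cause. Section 7.3.2 also allows romidepsin to be withheld for events regardless of relationship.
- The primary endpoint in 5.3.1 has no causality filter, so these events are counted in the main result.

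A reader might also infer that the romidepsin diary asks only about vaccination. It does not: 8.4.5 collects symptoms for at least 7 days after each infusion, and 5.7 has a physician assess causality for both diaries. The fault is confined to one investigator-attribution sentence, which matches the one in the vaccine diary section.

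These points narrow the consequence and they stand. They do not remove the contradiction between 9.1 and 9.4.3, the gap for non-serious grade 3 events at the 5.6 trigger, or the wrong product name. Investigators may depart from 9.4.3 in practice, but the rule should not depend on that.

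**Conclusion.** The point holds as an internal contradiction with a limited but real safety consequence. Sections 9.1 and 9.4.3 cannot both be applied to a reaction of unexpected nature. Read literally, 9.4.3 keeps non-serious grade 3 events of a new kind out of the 5.6 trigger. The sentence in 8.4.5 conflicts with 5.6, 7.3.2 and 10, but does not by itself prevent attribution to romidepsin.

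The size depends on how investigators would rate such events. At an assumed 10% rate in 24 participants, the trigger probability runs from 0.71 with full attribution, through 0.34 with half, to 0 under the literal text. The zero belongs to the most literal reading and is not a prediction. The upper figure assumes that every event is rated definite or probable and that all are clinically similar. The conclusion itself rests on reading the lists as cumulative, not on the assumed rates.

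**What to change.** 1. **Sections 9.4.3 and 9.1:** reconcile them so that an unlisted event with plausible timing and no better explanation can be rated related. For Probable and Possible, make the profile match supportive rather than required.
2. **Section 8.4.5:** name romidepsin in the attribution sentence. Record causality separately for MVA.HIVconsv and romidepsin, using one set of terms across 8.4.4, 8.4.5 and 9.4.3.
3. **Section 5.6:** reconcile the grade wording of the general statement with that of the numeric trigger.

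The cost is protocol wording and, where they carry the same text, matching changes to the case report form and related forms. No visit, sample or analysis is added. The downside is that more events may be rated related and sent to the committee.
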